#### Recruitment

Potentially eligible participants will be recruited by approaching consultants. They will be provided with a summary information sheet (see online supplementary appendix 1) and asked to reply with a list of patients under their care, who may be eligible to take part in the study and who have capacity to consent. Potentially eligible patients will be approached initially via their care team and invited to attend a primary meeting with the research team. After explaining the purpose of the meeting, each patient will be provided with a copy of the participant information sheet (PIS) and consent form (see online supplementary appendices 2 and 3). The PIS will detail the aim of the study and what their participation will involve and will inform them about how their data are kept confidential, their rights to withdraw and what will be carried out with the results. A minimum of 24 hours will be allowed for each patient to read through the information sheet and sign the consent form if they wish. Patient who are prepared to take part will be invited to attend a second meeting where the PIS will be explained to them thoroughly, any questions are answered and the written consent form is signed if it has not been already.

10.1136/bmjopen-2016-012710.supp1Supplementary appendices

#### Withdrawal of participants

Participants may be withdrawn from the study either at their own request or at the discretion of the investigator. If a patient is withdrawn from the study, consent will be sought from them to continue to obtain outcome data via their care team. Participants will be made aware that withdrawal will not affect their future care and that they should withdraw any previously collected data will not be erased and may be used in the final analysis.

#### Blinding and allocation concealment

This is an open label study.

#### Objectives and outcomes

The primary outcome is the proportion of people in open employment at 12-month follow-up. Open employment is defined as having a job for at least 1 day, paying at least the minimum wage in a mainstream setting and not specifically for people with disability or special needs. In order to capture other vocational aspects of employment, we will consider the following secondary outcomes: number of hours worked, number of days employed, number of hours spent in educational activities and number of days in education. We will also measure individual's self-worth, social integration, mental health, quality of life and recidivism.

Assessment of participants will take place in community forensic mental health team sites or their home address at baseline, 6 months and 12 months. Data collection will be completed by a research assistant using the following measures.

#### Baseline

Information concerning sociodemographics, diagnosis and offending history will be collected using a data collection tool specifically designed for the purpose of this study. Sociodemographic data will be obtained from case files, and later verified with patients, including age, gender, work history, number of years in education, qualifications, living situation (alone, with friends/relatives, supported accommodation, inpatient, other), age at first psychiatric contact and number of admissions to mental health institutions in life time. Information on diagnosis will be determined by approaching their care team. Offending history will be determined from case files. These baseline data will be used to describe the sample and to stratify the sample by work experience prior to conducting qualitative interviews.Brief Psychiatric Rating Scale (BPRS):^24^ This is a clinician/researcher rated scale which is widely used to measure psychiatric symptoms such as somatisation, anxiety, depression, hallucinations and others. It has 18 items and each item is measured on a scale of 1–7 (1=not present, 2=very mild, 3=mild, 4=moderate, 5=moderately severe, 6=severe and 7=extremely severe).Social Functioning Questionnaire (SFQ):^25^ This is a clinician/researcher rated scale used to assess an individual's social functioning. It is divided into five sections (self-care skills, domestic skills, community skills, social skills and responsibility), each containing eight items rated on a scale of 1–4. Of these, 10 items are marked as ‘Index Items' which can be used to derive a global measure of social functioning.Rosenberg's Self-Esteem Scale:^26^ This is a self-rated scale which measures self-esteem on 10 items. Each item is measured on a 4-point Likert scale—from strongly agree to strongly disagree.Work Limitations Questionnaire (WLQ):^27^ This is a self-rated questionnaire that measures the degree with which health problems impact on specific aspects of job performance and the productivity impact of these limitations. Respondents are asked to rate their performance on 25 specific job demands, yielding 4 work limitation demands: time management, physical demand, mental/interpersonal demands and output demands.Health-related quality of life, using SF-12v2^28^ and EQ5-D-3L:^29^ SF-12v2 is a 12-item self-rated questionnaire survey that measures functional health and well-being from the patient's perspective. EQ5-D is a self-rated measure of health status that provides a simple, generic measure of health for clinical and economic appraisal. It provides a descriptive profile and single index value for health status that can be used in economic evaluations of healthcare and to generate quality adjusted life years (QALYs) for comparative purposes.Client Service Receipt Inventory (CSRI):^30^ This scale is used to capture data on recent use of health and social care services, accommodation and living situation, income, employment and benefits. Data collected using the CSRI can be used to calculate total costs of care.

#### Six-month and 12-month follow-up

Information about employment activities will be collected by asking participants structured questions about these activities. Data on educational activities and other vocational activities such as training and volunteering will also be collected.Repeat measures for all other outcome measures, including BPRS, SFQ, Rosenberg's Self-Esteem Scale, WLQ, SF-12v2, EQ5-D and CSRI, will be obtained.Reoffending data: These will be based on self-report and Police National Computer records obtained via the locally agreed protocol between the police and NHS Trust.

#### Planned analysis and study data

Analysis will be conducted on a treatment allocated basis. We will describe recruitment and retention rates, ICCs of outcome measures (primary and secondary) and patterns of missing data. We will provide means and SDs for continuous outcomes and percentage proportions for categorical outcomes with CIs. Comparisons between the two arms will be made for the outcome measures administered to estimate potential magnitude of effect.

It must be acknowledged that estimating ICCs with small numbers of participants can potentially result in biased or imprecise estimates. Because of this, the feasibility study will not be the only source to estimate ICCs. Published or unpublished data of similar outcomes in adult mental health settings in the UK will also be used to estimate ICCs.

Monitoring of study data shall include confirmation of informed consent, source data verification, data storage and data transfer procedures, local quality control check and procedures, back-up and disaster recovery of any local databases and validation of data manipulation. All data held electronically concerning the primary outcome variables will be checked against the paper record for accuracy. Ten per cent of the remaining data will be checked in the same way. Where corrections are required, these will carry a full audit trail and justification.

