### Feasibility study (24 months)

#### Participants and study design

This study will recruit adult patients (male and female) who are over the age of 18 and who are currently on the caseload of the community forensic services. Patients who are unable to provide informed consent, who are not eligible to work in the UK, do not have an offending history, are currently in open employment or who do not wish to work will be excluded from this study.

This study employs a cluster RCT design. Clusters are defined according to clinical services in the community forensic services, which include four major divisions as follows: Cluster 1: City Community Forensic Service. Cluster 2: County Community Forensic Service. Cluster 3: City Personality Disorder Service. Cluster 4: County Personality Disorder Service.

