#### Randomisation: sequence generation

Randomisation of clusters was carried out by the trial statistician from the University of Leicester Clinical Trials Unit, allocating two clusters (City Community Forensic Service and the County Personality Disorder Service) to the intervention group (IPS+treatment as usual [TAU]). The remaining two clusters (County Community Forensic Service and City Personality Disorder Service) were allocated to the control group (TAU) (figure 1 for trial flow chart).

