#### Interventions

Group 1: Individuals assigned to the intervention group will receive IPS+TAU. Individuals will receive ongoing support from the employment specialist in accordance with the IPS principles. The employment specialist will work closely with patients assigned to IPS and begin job searches rapidly, based on their preferences. Colocation of the employment specialist within clinical teams will allow information about risks and past offending histories to be shared with employers (with patient's consent), health and criminal justice systems (for those concurrently under probation) and subsequently taken into consideration when matching job opportunities to individual preferences. The employment specialist will bridge the gap between the research team and the community forensic teams by virtue of being a member of both teams.

Group 2: Individuals assigned to the control group will not receive any IPS support but will continue to receive TAU from the community forensic services. TAU for patients who are part of the city or county forensic teams entails case management, where each individual is allocated a consultant and care coordinator. TAU for patients who are part of the City or County Personality Disorder teams will primarily be made up of therapy services providing specialised psychological interventions, including group therapy and attendance, at a therapeutic community. Neither groups are offered specialist employment support as part of TAU.

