#### Sample size

The sample size calculation was based on an assertion by Eldridge and Kerry^23^ that, for samples of 75–150 individuals, four clusters will be required to achieve reasonably precise 95% CI for intraclass correlation coefficient (ICC). We aim to recruit a total sample size of 76 individuals for the trial.

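### Service type and usual care differ across clusters, so a simple arm-versus-arm difference would partly reflect the forensic:PD mix if city and county recruit unequally; effects should be estimated within service type

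*Protocol article*

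**What the plan says.** All references are to the protocol article.

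- **Participants and study design** defines four clusters by crossing service type (community forensic, personality disorder) with area (city, county).
- **Randomisation: sequence generation** reports the draw as "allocating two clusters (City Community Forensic Service and the County Personality Disorder Service) to the intervention group". County forensic and city PD are the controls.
- **Interventions** gives two forms of TAU. One is described thus: "TAU for patients who are part of the city or county forensic teams entails case management". The other reads: "TAU for patients who are part of the City or County Personality Disorder teams will primarily be made up of therapy services". The section closes by saying that TAU offers specialist employment support to neither group.
- **Sample size** sets one target: "We aim to recruit a total sample size of 76 individuals for the trial". It gives no target by cluster or service type.
- **Planned analysis and study data** promises means, SDs and proportions with confidence intervals, then: "Comparisons between the two arms will be made for the outcome measures administered to estimate potential magnitude of effect". It does not mention service type.
- **Aims and objectives** says the estimates will be used to gauge plausible effect sizes and to size the full trial.

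**The concern.** The contrast of interest is IPS added to TAU against TAU alone. It isolates IPS only if the TAU and patient mix is the same in both arms. The diagonal allocation achieves this in numbers of clusters but not necessarily in numbers of patients. If the city services recruit more, the IPS arm fills with forensic patients and the control arm with PD patients; if the county services recruit more, the reverse happens. The arm totals can stay equal throughout, so they would give no warning.

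At stake is the effect size carried forward to the definitive trial. Given this allocation, more recruitment at the same city:county ratio would not shrink the shift.

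**Working it through.** **The plan's own figure.** The 76 rests on a cited rule (75–150 individuals, four clusters). The article gives no power, rates or ICC from which to derive it. It is consistent with the rule, and 76 / 4 = 19 per cluster on average, but the article does not require that split.

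**Mix by arm.** Write F for forensic and PD for personality disorder.

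- Forensic share, IPS arm = City F / (City F + County PD)
- Forensic share, control arm = County F / (County F + City PD)
- Shift in a simple arm difference = (gap between these shares) × (forensic minus PD difference in outcome)

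The gap is zero only when City F × City PD = County F × County PD, that is, when the city shares of the two services sum to 1.

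**Assumed values.** The article gives neither cluster sizes nor rates by service. Take 38 patients per service type, the same city share c in both, and no IPS effect. The forensic shares are then c and 1 − c, the gap is 2c − 1, and each arm has 38 patients.

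| City share c | Forensic share, IPS | Forensic share, control | Gap | Shift if types differ by 10 points | Shift if types differ by 20 points |
|---|---|---|---|---|---|
| 0.50 | 50% | 50% | 0 | 0 | 0 |
| 0.60 | 60% | 40% | 20 points | 2 points | 4 points |
| 0.70 | 70% | 30% | 40 points | 4 points | 8 points |

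Unequal service totals change little. With 50 forensic and 26 PD patients and c = 0.60, the shares are 30 / 40.4 = 74% and 20 / 35.6 = 56%. The gap is 18 points and the shift 1.8 or 3.6 points.

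**Exceptions.** Exact cancellation is possible: City F 40, County F 20, City PD 5 and County PD 10 (75 in all) give 40/50 = 20/25 = 80% forensic in both arms. Among integer splits of 76 with at least 5 per cluster and unequal city and county totals, 40 of 31,668 (0.13%) cancel exactly.

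**Precision.** Take 25% employed and clusters of 25 (City F), 13 (County F), 25 (City PD) and 13 (County PD), ignoring clustering.

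- Simple arm difference: SE = √(0.1875 × 2/38) = 0.099
- Average of the two within-type differences: SE = √(0.1875 × (1/25 + 1/13) / 2) = 0.105

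**What the average removes.** Let τ be the IPS effect and λ an additive city-minus-county effect.

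- City F − County F = τ + λ
- County PD − City PD = τ − λ
- Average = τ

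Service type cancels within each contrast, and λ cancels in the average. If the city effect differs by service (λF, λPD), the average is τ + (λF − λPD)/2, and four clusters cannot separate the two terms. Intercept, service type, location and arm use all four cluster-level degrees of freedom, so none is left to estimate between-cluster variation.

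**The case against.** The analysis section does not say that the comparison is pooled or unadjusted. A comparison within service type is also a comparison between arms, and an analysis plan that is not shown may specify one. This stands: a reader might infer that the article commits to a crude analysis, and it does not. What remains is that the article sets out two forms of TAU, this allocation and summary proportions and means by arm. Followed simply, that can give a shifted estimate.

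The allocation is as balanced as four clusters allow, with one service of each type and one of each area in both arms. This also stands. The shift needs unequal recruitment, which the article does not report, and the mirror-image draw would reverse its sign. It is a chance imbalance conditional on the draw, and the random allocation itself is not at fault.

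A reader might also infer that differing TAU undermines the primary outcome. The article does not support that: TAU lacks specialist employment support in both groups, so the arms are alike on the component of care closest to employment. Patient mix and other care may still affect employment and the symptom, functioning and quality-of-life scores.

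Finally, the study disclaims efficacy conclusions, and none of the four feasibility criteria in the Discussion uses an arm difference. That limits the consequence without removing it, because benchmarking effect sizes is a stated objective.

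**Conclusion.** The point holds in a limited form. Almost any city/county imbalance, though not every one, makes the forensic:PD mix differ between arms, and a simple arm difference then carries part of the difference between service types. With equal service totals, 60–70% city recruitment and a 10–20 point employment difference between types, the shift is about 2–8 points. All three inputs are assumptions. The shift is zero under equal recruitment and smaller than the standard error of about 10 points before clustering.

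The documents do not support a claim that the estimate will be biased, or biased by a known amount. They support the narrower conclusion that this source of error is foreseeable and can be removed with data already held. It is worth correcting and does not threaten the feasibility aims.

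**What to change.** In Planned analysis and study data, state that arm differences are estimated within service type (City Forensic against County Forensic; County PD against City PD), that their equally weighted average is the effect estimate, and that both contrasts are shown. State three limits: each single contrast is confounded with location; a service-by-location interaction cannot be removed; and with no spare between-cluster degree of freedom the estimate is descriptive.

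Report recruitment by cluster so that readers can see the mix. A quota per cluster is not advised: caseloads are not given, and it would constrain the recruitment that the study is meant to observe.

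The cost is a few sentences and no extra patients or data, since each participant's service is known. The standard error rises slightly when cluster sizes are unequal, from about 9.9 to 10.5 points at roughly a 2:1 city:county split.

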### Process evaluation (30 months)

Process evaluations will be carried out in parallel to the other two strands. The following three methods will be used:
Qualitative interviews with staff: a purposive sample reflective of a mix of backgrounds and experience will be selected for interview. Semistructured interviews will ask staff about their general views of IPS, barriers and facilitators to implementation. Interviews will continue until saturation is achieved. All interviews will be recorded and transcribed.Fidelity reviews: Fidelity of the IPS model will be assessed by an external facilitator (IPS Expert) at 6, 12 and 24 months using the supported employment fidelity scale.^31^ The aim of these reviews is to assess the extent to which the services follow the eight principles of IPS and to assess how well the employment specialist functions within the service.Qualitative interviews with patients: At 12 months, semistructured interviews will be completed with patients assigned to the intervention group who received IPS. A purposive sample reflecting a mix of work experience will be recruited. Specific questions will be asked about their general views of IPS, benefits and disadvantages of participating, barriers to implementation and acceptability. Interviews will continue until saturation is achieved. All interviews will be recorded and transcribed.

#### Planned analysis

Interviews will be recorded and transcribed verbatim with the interviewee's consent. The content of each transcript will be analysed using framework analyses, a validated analysis approach for policy research.^32^ The framework will be initially drafted using the key factors required to inform the ensuing study, such as barriers and facilitators. The framework will be revised iteratively as new themes appear, or original ones are removed due to lack of support by the qualitative data.

## Study management

### Research management group

A research management group has been established to manage the overall governance of the programme and day-to-day operations.

### Patient and public involvement

A patient and public involvement (PPI) reference group comprising patients, carers and representatives from Voluntary Sectors will be formed. The PPI reference group will meet quarterly throughout the duration of the programme. Group members will contribute meaningfully to all stages of the project and will provide valuable insight and advice. The PPI group will also be involved in helping to develop a leaflet and an implementation guide about IPS. Patients and carers of the group will be paid according to the Nottinghamshire Healthcare NHS Foundation Trust payment policy. Two members of the PPI will be part of the research management group and one PPI member will be involved in the process evaluation aspect of the study by conducting qualitative interviews with staff along with the research assistant, after they have been adequately trained.

### Ethics and dissemination

Should a protocol amendment be made that requires Research Ethics Committee (REC) approval, the changes in the protocol will not be instituted until the amendment and revised Informed Consent Forms (ICFs) and PIS have been reviewed and received approval from the REC and R&D departments. Should amendments be made to the final protocol which might affect a participant's participation in the study, continuing consent will be obtained using an amended ICF which will be signed by the participant. A guide to implementation of IPS in community forensic mental health settings will be developed based on the findings of this study. Final and interim reports will be prepared for project funders, the study sponsor and the clinical research network. Papers for peer-reviewed journals will be submitted for publication. Conference and event presentations will also be given.

### Adverse events

Decisions to stop the study will not be influenced by the analyses as these will be carried out at the end of the study period. However, any untoward serious incidents, including suicide and serious harm to others, will be reviewed and if there is any indication that these are linked to the intervention, the research will be stopped on the advice of the research management group.

### Records and source documents

Each participant will be assigned a trial identity code number for use on trial documents and electronic database. The list that links the identity codes to participants will be held securely by the chief investigator in accordance with the Nottinghamshire Healthcare NHS Foundation Trust Policies and procedures. The questionnaires will be treated as confidential documents and access shall be restricted to approved personnel. Electronic data will be encrypted and paper copies retained in a locked cabinet.

Source documents, which include questionnaires and interview transcriptions, shall be filed at the chief investigator’s site in a locked room. Only study staff will have access to study documentation.

